### Intervention

The EG will be trained with variable-priority instruction activities during the first 3 months (T1 to T2) and in the subsequent 3 months (T2 to T3) will be submitted to training with fixed-priority instructions activities. The GC will be trained under variable-priority instruction activities over the 6 months (T1 to T3). The detailed evolution of each of the groups can be found in Tables 1 and 2.

**Table 1 Tab1:** Detailed conceptual basis regarding foci, tasks, and respective progressions to structure the training protocol

Focus	Strategy	Task
1. Postural balance	a) Change the base of support	**Standing** 1) Normal standing (bipodal support with feet separated at shoulder width 2) Feet together (bipodal support with feet side by side) 3) Semi-tandem stance 4) Tandem stance 5) One leg support on the dominant leg 6) One leg support on the non-dominant leg
		**Walking** 7) Semi-tandem 8) Tandem
	b) Displace the center of mass in different directions and with different bases of support	1) Sequentially perform F1a (1–6) by first laterally moving the trunk with shoulder abducted at least above 60 degrees 2) Sequentially perform F1a (1–6) by first laterally moving the trunk with the arms alongside the body
	c) Reach the body limits of stability and holding them at this point	1) Sequentially perform F1a (1–6) by first laterally moving the trunk with shoulder abducted at least above 60 degrees 2) Sequentially perform F1a (1–6) by first laterally moving the trunk with the arms alongside the body
	d) Change the somatosensation input (stability/complacency of the support surface)	Standing on different surfaces (rigid, soft or rough) 1) Sequentially perform F1a (1–6)
		Walking on different surfaces (rigid, soft or rough) 2) Sequentially perform F1a (7–8)
	e) Change the vision input	Standing with eyes closed 1) Sequentially perform F1a (1–6)
		Walking with eyes closed 2) Sequentially perform F1a (7–8)
2. Muscle strength and power, and postural balance during stationary activities performance	a) Standing still in a semi-squatting posture	1) Increase the time staying in this posture
	b) Weight-loaded in a single-leg stance	1) Gradually increase the standing time in this posture
	c) Sit to stand	1) Increase the number of cycles per seconds (starting at a frequency of one cycle per second)
3. Pattern, agility, power, response time, and postural balance during walking	a) Increase the stride length and walking speed	1) Gradually increase the stride length using hula hoops, traffic cones, climbing ladder, marking and boxes positioned on the floor 2) Gradually increase the walking speed 3) Gradually increase and decrease the forward and backward walking acceleration while a command (rapid or slow) is proffered by the instructor
	b) Change the walking directions	1) Forward, backward, left, right, and turning around 2) Gradually reduce the interchange time between different directions 3) Spinning and spinning-walking
	c) Change the stability/complacency of the support surface	1) Sequentially perform F1a (7–8) first on a stable surface (floor) and then on an unstable one (foam cushion or mats) 2) Randomly perform F1a (7–8) first on a stable surface (floor) and then on an unstable one (foam cushion or mats)
	d) Change the level of walking	1) Increase step, obstacle, and ramp negotiation and the alternance between the obstacles
4. Secondary motor tasks performance	a) Manipulative tasks while walking	1) Closing buttons and zippers while walking; taking the wallet, handkerchief, or coins out pocket 2) Transportation and manipulation of the object
	b) Coordination tasks while walking	1) Contour a ball around the own trunk 2) Bouncing a ball on the ground 3) Clap the hands according to a command
	c) Confidence in balance-required tasks	1) While in a stationary posture, achieve and pick up objects from a raised height 2) While walking, bend laterally and/or anteriorly the trunk at the limits of stability in order to achieve and pick up objects with different sizes, quantities, and locations (on a bench or on the ground)
	d) Maneuvering traffic	1) Avoiding collision with the other participants of the group while walking
5. Cognitive tasks	a) Working memory	1) Phonological fluency: Say words according to the letter they begin with (such as” F″,” A”, or” S″) 2) Semantic fluency: Say words according to a category (such as” animals”,” fruits” or “supermarket shopping list”, and sometimes” verbs” v” nouns”), randomly chosen by the instructor 3) N-back and n-forward problem solving (e.g., subtracting or summing *n* from an established number) 4) Auditory forward digit span: Remember as many as possible of the number/letter forward sequence, you were told 5) Auditory backward digit span: Remember as many as possible of the number/letter back sequence, you were told 6) Visual forward digit span: Remember as many as possible of the number forward sequence shown to you by means of cardboard 7) Visual backward digit span: Remember as many as possible of the number/letters backward sequence shown to you by means of cardboard
	b) Perceptual performance	1) Quickly count the amount of objects/dots shown in a paperboard 2) Quickly identify the number of points/objects on a paperboard (among other different objects shown on the data show projection on the wall)
	c) Mental tracking	1) Count (and say after) how many times a word (e.g. “cat”) was said in a story about this subject (cats)
	d) Reaction time	1) React as fast as possible (e.g. clap the hands, or say “yes”) when a certain word was said or sound was emitted 2) React as fast as possible (e.g. clap the hands, or say “yes”) when a cardboard with a dot, figure or letter was shown 3) Go/No-go visual reaction time (walk when a “go” cardboard was shown and stop walking when a “stop” cardboard was shown)
	e) Selective reaction time	1) Say “yes” when hearing “strawberry” but say nothing when hearing another sort of fruit 2) Increase walking speed when hearing “orange”, decrease walking speed when hearing “banana”, say “yes” when hearing “strawberry”, but say nothing or change the walking condition when hearing another sort of fruit
	f) Executive performance	1) Perform steps according to arrows directions: identify the direction of the arrow tips and perform step as fast as she/he can 2) Color reading interference (a variant of the classic Stroop test): Say the printed color and not the color name that the word was printed (and presented in the wall by data show projection) 3) View the arrow and commands direction projected on a screen by means a data show equipment and quickly transport yourself to the presented direction /command 4) Simultaneously pronouncing and stepping on numbers stamped on a rug

**Table 2 Tab2:** Detailed scheme on the association between the foci, strategies, and task training for the control and experimental groups

Stage	Timeline (week)	Foci, strategies, and tasks	
		CG	EG
1	1st to 3rd	**F1**a (1–8), **F1**b (1–2), **F1**c (1–2), **F2**a (1), **F2**b (1), **F2**c (1), **F3**a (1–2), **F3**b (1), **F3**c (1), **F5**a (1–2)^**a**^	Idem to the CG
2	4th to 6th	**F1**a (1–8), **F1**b (1–2), **F1**c (1–2), **F1**d (1–2), **F1**e (1), **F2**a (1), **F2**b (1), **F2**c (1), **F3**a (1–3), **F3**b (1–2), **F3**c (1–2), **F4**a (1–2)^**a**^, **F4**b (1)^**a**^, **F5**a (1–3)^**a**^	Idem to the CG
3	7th to 9th	**F1**a (1–8), **F1**b (1–2), **F1**c (1–2), **F1**d (1–2), **F1**e (1–2), **F2**a (1), **F2**b (1), **F2**c (1), **F3**a (1–3), **F3**b (1–2), **F3**c (1–2), **F3**d (1), **F4**a (1–2)^**a**^, **F4**b (1–2)^**a**^, **F5**a (1–3), **F5**d (1–3)^**a**^	Idem to the CG
4	10th to 12th	**F1**a (1–8), **F1**b (1–2), **F1**c (1–2), **F1**d (1–2), **F1**e (1–2), **F2**a (1), **F2**b (1), **F2**c (1), **F3**a (1–3), **F3**b (1–3), **F3**c (1–2), **F3**d (1), **F4**a (1–2)^**a**^, **F4**b (1–3)^**a**^, **F4**c (1)^**a**^, **F5**a (1–4)^**a**^, **F5**e (1–2)^**a**^	Idem to the CG
5	13th to 15th	**F1**a (1–8), **F1**b (1–2), **F1**c (1–2), **F1**d (1–2), **F1**e (1–2), **F2**a (1), **F2**b (1), **F2**c (1), **F3**a (1–3), **F3**b (1–3), **F3**c (1–2), **F3**d (1), **F4**a (1–2)^**a**^, **F4**b (1–3)^**a**^, **F4**c (1–2)^**a**^, **F5**a (1–7)^**a**^, **F5**b (1)^**a**^, **F5**e (1–2)^a^	**F1**a (1–8), **F1**b (1–2), **F1**c (1–2), **F1**d (1–2), **F1**e (1–2), **F2**a (1), **F2**b (1), **F2**c (1), **F3**a (1–3), **F3**b (1–3), **F3**c (1–2), **F3**d (1), **F4**a (1–2)^**b**^, **F4**b (1–3)^**b**^ **F4**c (1–2)^**b**^, **F5**a (1–7)^**b**^, **F5**b (1)^**b**^, **F5**e (1–2)^**b**^
6	16th to 18th	**F1**a (1–8), **F1**b (1–2), **F1**c (1–2), **F1**d (1–2), **F1**e (1–2), **F2**a (1), **F2**b (1), **F2**c (1), **F3**a (1–3), **F3**b (1–3), **F3**c (1–2), **F3**d (1), **F4**a (1–2)^**a**^, **F4**b (1–3)^**a**^, **F4**c (1–2)^**a**^, **F5**a (1–7)^**a**^, **F5**b (1–2)^**a**^, **F5**c (1)^**a**^, **F5**d (1–2)^**a**^, **F5**e (1–2)*****	**F1**a (1–8), **F1**b (1–2), **F1**c (1–2), **F1**d (1–2), **F1**e (1–2), **F2**a (1), **F2**b (1), **F2**c (1), **F3**a (1–3), **F3**b (1–3), **F3**c (1–2), **F3**d (1), **F4**a (1–2)^**b**^, **F4**b (1–3)^**b**^, **F4**c (1–2)^**b**^, **F5**a (1–7)^**§**^, **F5**b (1–2)^**b**^, **F5**c (1)^**b**^, **F5**d (1–2)^**b**^, **F5**e (1–2)^**b**^
7	19th to 21st	**F1**a (1–8), **F1**b (1–2), **F1**c (1–2), **F1**d (1–2), **F1**e (1–2), **F2**a (1), **F2**b (1), **F2**c (1), **F3**a (1–3), **F3**b (1–3), **F3**c (1–2), **F3**d (1), **F4**a (1–2)^**a**^, **F4**b (1–3)^**a**^, **F4**c (1–2)^**a**^, **F5**a (1–7)^**a**^, **F5**b (1–2)^**a**^, **F5**c (1)^**a**^, **F5**d (1–3)^**a**^, **F5**e (1–2)^**a**^, **F5**f (1–2)^**a**^	**F1**a (1–8), **F1**b (1–2), **F1**c (1–2), **F1**d (1–2), **F1**e (1–2), **F2**a (1), **F2**b (1), **F2**c (1), **F3**a (1–3), **F3**b (1–3), **F3**c (1–2), **F3**d (1), **F4**a (1–2)^**b**^, **F4**b (1–3)^**b**^, **F4**c (1–2)^**b**^, **F5**a (1–7)^**§**^, **F5**b (1–2)^**b**^, **F5**c (1)^**b**^, **F5**d (1–3)^**b**^, **F5**e (1–2)^**b**^, **F5**f (1–2)^**b**^
8	22nd to 24th	**F1**a (1–8), **F1**b (1–2), **F1**c (1–2), **F1**d (1–2), **F1**e (1–2), **F2**a (1), **F2**b (1), **F2**c (1), **F3**a (1–3), **F3**b (1–3), **F3**c (1–2), **F3**d (1), **F4**a (1–2)^**a**^, **F4**b (1–3)^**a**^, **F4**c (1–2)^**a**^, **F4**d (1)^**a**^, **F5**a (1–7)^**a**^, **F5**b (1–2)^**a**^, **F5**c (1)^**a**^, **F5**d (1–3)^**a**^, **F5**e (1–2)^a^, **F5**f (1–4)^a^	**F1**a (1–8), **F1**b (1–2), **F1**c (1–2), **F1**d (1–2), **F1**e (1–2), **F2**a (1), **F2**b (1), **F2**c (1), **F3**a (1–3), **F3**b (1–3), **F3**c (1–2), **F3**d (1), **F4**a (1–2)^**b**^, **F4**b (1–3)^**b**^, **F4**c (1–2)^**b**^, **F4**d (1)^**b**^, **F5**a (1–7)^**b**^, **F5**b (1–2)^**b**^, **F5**c (1)^**b**^, **F5**d (1–3)^**b**^, **F5**e (1–2)^**b**^, **F5**f (1–4)^**b**^

Note: *CG* Control group (dual-task training with variable priority attention), *EG* Experimental group (dual-task training with progression of activities from variable to fixed priority attention); ^a^Secondary cognitive or motor task will always be interspersed with dual tasks with variable priorities; ^b^Secondary cognitive or motor task will always be performed simultaneously with dual tasks with fixed priorities

Participants of both groups must attend at least 75% [26] of the 60-min training sessions, which will occur twice a week for 24 weeks. Each of the 48 group training sessions (maximum of 15 participants in each group) will include: i) a warm-up (10 min) with supervised walking on a flat surface and static postural balance exercises, ii) training (four stations, 10 min each, total of 40 min) for protocol execution, and iii) a cool-down, including breathing exercises and global muscle stretching (10 min). The principles of this training will follow recommendations from previous studies [26–29]. Interventions of each group will be supervised by a physical therapist with experience in ​​dual-task exercises and by four undergraduate students of the final year’s physical therapy course. Adherence monitoring will be done by signature in the presence table in each training session. Concomitant exercise programs for postural balance are not permitted during the trial for both groups.

The dual-task training program is designed based on activities described by Wollesen et al. [29] as well as the studies by Strouwen et al. [30] and Zhao and Pak-Kwongchung [31]. Table 1 presents the conceptual basis that will be used to structure the dual-task protocol training. The progression of the protocol will be based on eight foci (F1–F8), while strategies will progress in intensity and degree of difficulty; the tasks will be determined by associating the respective foci (F1–F8) with the strategies. This will allow for the graduation of the challenge level at each training stage regarding participants’ postural control and gait pattern.

Table 2 shows the methodology that will be applied to the progression of the exercises, structured according to the conceptual basis described in Table 1. This protocol will be performed in a circuit composed of hula hoops, ropes (in a straight line and zigzagging), an agility ladder, traffic cones, steps, cardboard boxes, and other obstacles arranged on the floor (stable surface) or on mattresses (unstable surface), depending on the aim of each training stage. Before starting each session, the instructors will explain all exercises with additional verbal feedback to improve task performance.

### Adverse events

All adverse events will be self-reported by the participant to the principal researcher. An adverse event will be defined as any unfavorable or unintentional health-related event (sign, symptom, syndrome, or disease) that develops or worsens during the study period. These events will be monitored closely until a resolution or stabilization is achieved, or until it has been shown that the study intervention is not the cause of the event. According to the recent epidemiologic data of the Brazilian Longitudinal Study of Aging (ELSI-Brazil) [32], if falls incidences during the training session are greater than 25% with 3% resulting in a hip or femur fracture, the study will be interrupted. The decision to do so will be immediately reported to the research team, and the local research ethics committee will be notified. If there is a fall episode during training that requires medical attention or any other complication during the execution of the study, the mobile emergency response service will be contacted so that the participant can be promptly referred to the local university hospital.

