### Sample size

Gait speed (primary outcome) under fixed-priority dual tasks was used to calculate the sample size [18]. We adopted a minimal clinically important difference of 0.05 m/s, an effect size of 0.20 [19], a power of 95% (1 - β), an alpha of 0.05, and a design of *F*-statistic repeated measures with a within- and between-subjects interaction effect. Forty-eight participants were initially obtained as the study sample total. Taking into account a 20% sample loss, 60 participants will be assessed and allocated to the study by a ratio of 1:1. The sample size was calculated using the G*Power 3 [20].

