### Eligibility criteria

Participants of both sexes between the ages of 60 and 80 years will be included in this study. For security reasons, only individuals presenting a score of ≥52 (up to a maximum of 56) on the Berg Balance Scale [18], a score of ≥24 (up to a maximum of 30) on the Mini-Mental State Examination [21], and who are able to walk uninterrupted for a distance of 10 m at a self-selected velocity of at least 1 m/s without assistance from another person, cane, or walker will be included. Potential participants will be excluded if they (i) have any contraindication to postural balance and cognitive exercise, (ii) have fallen two or more times in the last 12 months, (iii) participate or have participated in any regular or structured physical exercise program two or more times per week in the last 6 months, (iv) have a chronic health condition for which exercise is contraindicated, (v) have had any upper or lower limb fracture in the last 6 months [22], (vi) have evidence of any surgical procedures to the knees, ankles, or hips or have had muscle damage in the last 6 months [23], (vii) have self-reported uncontrolled diabetes, (viii) no able to speak and understand the Portuguese language, and (ix) refusal to give informed consent.

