### Monitoring

Data monitoring committee (DMC) will be formed by the researchers [name], and [name], which are independent of the sponsor and competing interests. Further details about the DMC can be achieved by sending an e-mail to [contact].

[name] and [name] will compose the interim analyses committee in order to make decisions about study stopping or terminating the trial.

Monthly, data collecting, assessing, reporting, and managing solicited and spontaneously reported adverse events and other unintended effects of trial interventions will be carried out by [name] and [name], which are independent of investigators and the sponsor.

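### The only numeric safety stopping rule counts a hip or femur fracture only when in-session falls also exceed 25%, so a fracture below that fall level does not meet the written trigger.

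*Protocol article*

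**What the plan says.** The Adverse events section of the protocol article holds the only numeric stopping criterion. Interruption of the study follows "if falls incidences during the training session are greater than 25% with 3% resulting in a hip or femur fracture". Nothing in the section says whether the 25% refers to participants or fall events, to the whole trial, one arm or one session, or whether the 3% is a share of fallers or of participants. It also says that each event is followed closely until it resolves, stabilises or is shown not to come from the intervention, and that a fall needing medical attention leads to emergency care and hospital referral.

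The Sample size section states that "60 participants will be assessed and allocated to the study by a ratio of 1:1". Under Intervention, group sessions hold at most 15 participants, are supervised, and run to 48 in all, "which will occur twice a week for 24 weeks". Eligibility excludes people who "have fallen two or more times in the last 12 months".

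The Monitoring section names a data monitoring committee. It provides that "Monthly, data collecting, assessing, reporting, and managing solicited and spontaneously reported adverse events" is done by persons independent of the investigators and sponsor. It also names two researchers who "will compose the interim analyses committee in order to make decisions about study stopping or terminating the trial", and prints no criterion for them. Table 3 schedules adverse-event recording as needed throughout.

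**The concern.** A hip or femur fracture during training is the most serious harm that the rule names. A reader would expect it to prompt a look at the trial by itself. As worded, it is a second condition that matters only once more than a quarter have fallen. The fall limb is by far the harder of the two to reach, so it decides whether the rule can be met. Excluding repeat fallers and supervising sessions make a high fall count less likely, and so make the rule less likely to be met.

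At stake is whether the single written criterion would send a training-related fracture to the people empowered to pause the trial. If it would not, that step rests on judgement alone, and the printed threshold could even be cited as a reason to continue.

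**Working it through.** **Inputs from the protocol article.** Rule: falls above 25% together with 3% fractured (Adverse events). Allocated: 60 at 1:1, so 30 per arm (Sample size). Session maximum: 15 (Intervention). Schedule: 2 sessions a week, 48 in all (Intervention).

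**Reproducing the plan's own figure.** The rule has no derived figure, but the denominator of 60 can be checked. For a repeated-measures within-between interaction with 2 groups, 5 time points, f = 0.20 and alpha = 0.05, assuming a correlation of 0.5 and sphericity (neither is stated), N = 48 gives power 0.952. That agrees with "Forty-eight participants were initially obtained as the study sample total". Then 48/(1 − 0.20) = 60, as stated.

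**Step 1: the fall limb.** The threshold is the smallest whole number strictly above 25% of the denominator.

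| Denominator | 25% of it | Fallers needed |
|---|---|---|
| 60 (all participants) | 15.0 | 16 (26.7%) |
| 30 (one arm) | 7.5 | 8 |
| 15 (one full session) | 3.75 | 4 |

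**Step 2: the fracture limb.** As a share of fallers, 0.03 × 16 = 0.48 and 0.03 × 33 = 0.99, so one fracture is enough for 16 to 33 fallers. One fracture is also enough at 8 fallers (0.24) and at 4 (0.12). If the 3% is of all participants, 0.03 × 60 = 1.8 and two fractures are needed. On the share-of-fallers reading, one fracture among 15 fallers would already be 6.7%, well over 3%, and would still not count because 15/60 is not above 25%.

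**Step 3: how often this matters.** Assumptions: 60 independent participants, each faller counted once, X ~ Bin(60, p) fallers, and F given X ~ Bin(X, q) with a fracture.

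- Any fracture: P(F ≥ 1) = 1 − (1 − pq)^60. For p = 0.10 and q = 0.03 this is 1 − 0.997^60 = 0.165. For p = 0.15 and q = 0.03 it is 1 − 0.9955^60 = 0.237.
- Rule met: P(X ≥ 16 and F ≥ 0.03X), summed over X.

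| Fall risk / share of fallers fractured | At least one fracture | Rule met |
|---|---|---|
| 5% / 1% | 0.030 | <0.0001 |
| 5% / 3% | 0.086 | <0.0001 |
| 10% / 3% | 0.165 | 0.0001 |
| 15% / 1% | 0.086 | 0.002 |
| 15% / 3% | 0.237 | 0.005 |
| 25% / 3% | 0.363 | 0.182 |

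The fall limb alone is reached with probability 0.0002 at 10%, 0.014 at 15% and 0.131 at 20% fall risk. If two fractures are required (3% of 60), the rule is met with probability 0.0012 at 15%/3% and 0.044 at 25%/3%. Two or more fractures in the trial are rare (0.014 at 10%/3%, 0.030 at 15%/3%), so the realistic missed case is a single fracture.

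**The case against.** **The cut-off is not fixed by the text.** A reader might infer that, at n = 60, a fracture among 15 or fewer fallers can never meet the rule. The documents do not support that. If a session or an arm was meant, 4 of 15 or 8 of 30 would do, and if fall events are counted, repeat falls could pass 25% with fewer than 16 people. This objection stands. What does not depend on the denominator is that a fracture below the fall threshold does not count.

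**Oversight exists.** A reader might also infer that a fracture would go unnoticed, that the trial could not be stopped, or that about a month of sessions (2 × 52/12 = 8.7) would pass first. None of this follows. Sessions are supervised, every event is followed individually with attention to cause, Table 3 has events recorded as needed, and a committee may stop the trial on judgement. Monthly is the stated rhythm for independent handling of events, not a required wait. This stands too and limits the consequence. But none of these provisions prints a trigger for trial-level review after a fracture.

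**The article is condensed.** Triggers may be set out in committee documents not shown. That would excuse a missing rule. Here a rule is printed, and the objection is to how its two limbs are joined.

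**The risks are assumed.** Only 25% and 3% come from the document. At 5%/1% the chance of any fracture is only 0.03, and at 25%/3% the comparison is shaped by placing the fall risk on the threshold itself. The probabilities therefore illustrate the point; the conditional wording establishes it.

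**Conclusion.** The point holds as a defect in the written trigger and no further. The one numeric safety rule makes a hip or femur fracture count only when in-session falls also exceed 25%, under every denominator considered. On the 60-participant reading, with assumed risks of 10%/3% and 15%/3%, a fracture occurs with probability 0.165 and 0.237, and the rule is met with probability 0.0001 and 0.005.

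These figures rest on independent participants, each faller counted once, the 3% taken as a share of fallers, and fall and fracture risks that the documents do not give. They compare a fracture with the rule being met, not with review taking place, because the committee can act on judgement. The correction is worth making because it is cheap and concerns participant safety. Confidence is moderate, since the intended unit and denominator are unknown.

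**What to change.** Add to the Adverse events section: *Any training-related hip or femur fracture leads to a pause and prompt review by the interim analyses committee.* This should apply whatever the number of falls.

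The sponsor should also state the unit (participants or events) and the denominator (trial, arm or session) intended for the 25% and the 3%. A count of 16 of 60 should not be written in on the sponsor's behalf: if an arm or a session was meant, it would loosen the rule from 8 of 30 or 4 of 15.

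Cost: one sentence, one clarification and an ethics committee notification. No new data are needed, since falls and adverse events are already recorded. The downside is an occasional pause, with probability about 0.03 (5%/1%) to 0.24 (15%/3%) under the assumptions above. Each one-week pause would cost 2 of 48 sessions (4.2%) if they are not made up. A pause is not a termination.
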